## Abstract

**Background:**

Chronic obstructive pulmonary disease (COPD) is a global public health problem. It is the third-leading cause of death in the world, the fourth leading cause of death in Kazakhstan, and is strongly associated with smoking. Smoking cessation reduces the severity of respiratory symptoms and COPD exacerbations. Heated tobacco products, such as HeatSticks heated by the iQOS device, a smoke-free electronic device, may serve as less risky alternatives to conventional combustible cigarettes.

**Objective:**

The purpose of this study is to evaluate frequency of exacerbations, respiratory symptoms, physical exercise intolerance, and abnormal lung functions, as well as other parameters and comorbidities among men and women aged 40-59 residing in Almaty, Kazakhstan, who use iQOS with HeatSticks compared to smokers of conventional cigarettes.

**Methods:**

This is a 5-year single-center cohort observational study. It includes two cohorts of participants consisting of men and women aged 40-59 residing in the city of Almaty, Kazakhstan: (1) smokers of combustible cigarettes (control group) and (2) users of iQOS with HeatSticks (exposure group). The study has baseline and periodic (ie, annual) comprehensive clinical assessments, as well as continuous COPD case-finding activities and registration of acute respiratory exacerbations over the course of the 5-year observation period. Study measures include spirometry, chest computed tomography, electrocardiography, physical exams, laboratory testing of serum for biomarkers of inflammation and metabolic syndrome, anthropometry, and the 6-minute walk test. Information about COPD symptoms will be collected using the COPD Assessment Test.

**Results:**

Participant recruitment began December 2017, and enrollment is expected to last until late summer 2018.

**Conclusions:**

This is the first cohort observational study in Kazakhstan to assess differences in lung function between users of the heated tobacco product, iQOS with HeatSticks, and smokers of conventional combustible cigarettes. The study results will add to knowledge on whether switching from combustible cigarettes to iQOS with HeatSticks affects respiratory symptoms and diseases, including the development and progression of COPD.

**Trial Registration:**

ClinicalTrials.gov NCT03383601; https://clinicaltrials.gov/ct2/show/NCT03383601 (Archived by WebCite at http://www.webcitation.org/72BYoAKxa)

**International Registered Report Identifier (IRRID):**

PRR1-10.2196/10006

## Introduction

Chronic obstructive pulmonary disease (COPD), the fourth leading cause of death in Kazakhstan, is a global public health problem. It is the third leading cause of death globally, accounting for 3.2 million deaths worldwide in 2015 [1]. In Kazakhstan, an expected 1.4 million people may have COPD based on estimations from neighboring countries [2]. COPD negatively affects the quality of life and is a major health care burden [3]. It is the third leading cause of hospital readmission within 30 days [4]. Cigarette smoke is the most common risk factor for COPD [5]. COPD is traditionally defined by airflow obstruction and includes emphysema, gas trapping, and chronic bronchitis [6]. Systemic effects (eg, on heart and muscles) and associated comorbidities (eg, heart failure, metabolic disorders, sleep apnea syndrome, and depression) may complicate the course of disease, posing challenges in the management of COPD [7-9].

Recently, we conducted a cross-sectional study of COPD among men and women aged 40-59 who currently smoke cigarettes, do not smoke, and stopped smoking 1-5 years ago [10]. We demonstrated that based on the COPD Assessment Test (CAT), respiratory symptoms are common in current smokers who have spirometric values that are generally considered to be within the normal range. We identified a relatively low percentage of participants with obstructed respiratory functions on spirometry. It was higher among current smokers (5.5%) compared to former and nonsmokers (3% among both groups). We found that 42% of current smokers had COPD symptoms based on a CAT score of ≥10—a prevalence of symptoms that was far greater than that among former smokers and controls who never smoked (17% and 12.5%, respectively). In addition, smoking cessation significantly reduced functional exercise incapacity, that is, inability to walk 450 meters within 6 minutes in the 6-Minute Walk Test (6MWT; 11% among ex-smokers compared to 16.7 % among current smokers).

Our findings agree with and extend previously published data, including studies that document exacerbation-like events in smokers without airway obstruction [11,12]. Many current or former smokers, despite normal spirometry values, have clinical symptoms and findings that are consistent with a chronic lower respiratory disease similar to COPD. In addition, these symptomatic current or former smokers with preserved pulmonary function had a higher risk of respiratory exacerbations or abnormalities on a chest computed tomography (CT) scan or shorter 6-minute walk distances than asymptomatic current or former smokers with preserved pulmonary function. The CAT is a clinically useful tool that can identify smokers at risk for exacerbations [11].

Smoking cessation reduces the severity of respiratory symptoms and slows the mean rate of lung function decline but does not eliminate the risk of progressive lung disease [13]. In our cross-sectional study, we demonstrated negative association between smoking cessation and activity limitations and positive association between smoking of combustible cigarettes and evidence of airway disease. As compared to never-smokers, current and former smokers had elevations in all components of the CAT score: cough, phlegm, chest tightness, breathlessness going up hills/stairs, activity limitation at home, confidence leaving home, sleep, and energy. At the same time, those parameters were lower among those who stopped smoking 1-5 years ago compared to those who continued smoking.

Alternative tobacco products to conventional cigarettes have come on the global market with claims of being “modified risk” tobacco products. These electronic devices heat the tobacco instead of burning it to supposedly deliver fewer toxins than cigarette smoke. These heated tobacco products include HeatSticks, a specially designed heated tobacco unit that contains tobacco heated up to 350˚C by the iQOS device. The product was developed by Philip Morris International, Inc, which claims that the vapor from HeatSticks heated by the iQOS device contains 90%-95% less harmful and potentially harmful compounds and is 90%-95% less toxic than the smoke of a reference combustible cigarette. Results of a 3-month reduced-exposure study in Japan showed that a reduction in 15 biomarkers of exposure to 15 harmful and potentially harmful compounds for the smokers who switched to a heated tobacco product for the duration of the study approaches the reduction in the same biomarkers for smokers who quit for the duration of the study [14]. Polosa et al showed that electronic cigarettes (ie, a battery-operated device that emits doses of vaporized nicotine) might improve COPD outcomes, including subjective respiratory outcomes as well as annual exacerbation rate [15]. We hypothesize that participants who use iQOS with HeatSticks will have less prevalent presence of respiratory symptoms, have better functional exercise capacity, and experience fewer exacerbations compared to those who smoke combustible cigarettes.

## Methods

### Study Design

The goal of this study is to evaluate whether the presence of respiratory symptoms, functional exercise incapacity, and COPD exacerbation rate across time are the same between the exposure group (users of iQOS with HeatSticks) and the control group (smokers of combustible cigarettes) through hypothesis testing.

In addition to this confirmatory goal, we would like to explore trends in spirometry results, chest CT scan results, prevalence of impaired quality of life, metabolic syndrome, abnormalities found by electrocardiography (ECG), physical exams, and serum lab tests among those who use iQOS with HeatSticks and those who currently smoke combustible cigarettes.

Exacerbation history will be collected prospectively (every 3 months) with the use of the adapted version of our proprietary SymptoMaster (Web, iOS, and Android) [16], and Medintel (Web) apps [17]. Symptoms history will be analyzed by clinical investigators. Should there be symptoms identified that are relevant to COPD, clinical investigators will approach health care organizations (serving participants in primary health care catchment area) to obtain ambulatory records of the use of antibiotics and/or systemic glucocorticoids or a health care utilization event.

Our primary confirmatory outcome variables are (1) presence of respiratory symptoms defined by CAT≥10, (2) functional exercise incapacity, and (3) exacerbation rate. The main exposure variable is smoking status (users of combustible cigarettes and users of iQOS with HeatSticks). The study groups are defined as:

Individuals (men and women) aged 40-59 years (inclusive) with a minimum of 10 pack-year smoking history who switched to and predominantly use the heated tobacco product iQOS with HeatSticks (exposure group). Predominant use of iQOS with HeatSticks is defined as >70% use.Individuals (men and women) aged 40-59 years (inclusive) who are currently smoking combustible cigarettes with a minimum of 10 pack-year smoking history (control group)

Pack-years will be calculated by taking the average number of cigarettes smoked per day divided by 20 and multiplied by the number of years smoked.

The Global Initiative for Chronic Obstructive Lung Disease (GOLD) definition describes COPD exacerbations as an acute worsening of respiratory symptoms that results in additional therapy [18]. They are classified as mild (ie, treated with short-acting bronchodilators only), moderate (ie, treated with short-acting bronchodilators and/or oral corticosteroids), or severe (ie, patient requires hospitalization or emergency room visit). Severe exacerbations may also be associated with acute respiratory failure. Once signs of exacerbations are identified, special efforts will be made by the Kazakhstan Academy оf Preventive Medicine (KAPM) clinical investigators, coordinators, and the principal investigator to establish their significance (ie, mild, moderate, or severe), and relevance to COPD.

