### Sample Size Calculation

Based on the results of the cross-sectional study, we demonstrated that smoking cessation alleviates activity limitations and airway disease caused by smoking of combustible cigarettes. This is evidenced by the prevalence of a CAT score of ≥10 among those who stopped smoking during the past 1-5 years at 17% compared to 42.8% among current smokers, and reduced inability to walk 450 meters within 6 minutes on 6MWT (11% compared to 16.7% among current smokers).

We hypothesize that switching from combustible cigarettes to iQOS with HeatSticks may reduce the risk of respiratory exacerbation and other COPD manifestations, somewhat similar to the effects of smoking cessation observed in the cross-sectional study.

In the cross-sectional study, duration of smoking abstinence in the second (ex-smoker) study group varied from 1-5 years. This is comparable with the length of the cohort study (5 years) that we propose. Therefore, we can use estimates of the outcome variables derived from the cross-sectional study to calculate required sample sizes that can identify statistically significant differences.

We suggest implementing a matched-pair cohort study design where a pair contains one iQOS with HeatSticks user and two conventional cigarette users matched by gender, age, education, and baseline exposure level (number of pack-year). By selecting this study design, we take into account the limited number of iQOS users from which the first (exposure) cohort is planned to be recruited.

To perform sample size calculation, we will assume that the associations we observed in the cross-sectional study between primary confirmatory outcomes and the smoking status (ex-smokers vs current combustible cigarette smokers) will be the same for iQOS users as compared to combustible cigarette smokers at the final visit after 5 years:

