At the final visit, the odds ratio of association between the exposure and CAT score of ≥10 will equal 0.27 and a CAT ≥10 prevalence will be 42.8% in the control group.At the final visit, odds ratio of association between the exposure and inability to walk 450 meters on the 6MWT will equal 0.62 and a 6MWT <450 meters prevalence will be 16.7% in the control group.At the final visit, rate ratio of association between the exposure and exacerbations will equal 0.5 and annual exacerbation rate will be 0.1 in the control group based on conservative estimations from Woodruff et al [10]. We also assume that these associations will increase steadily from 1 to the above-indicated values. Sample size calculations for three primary confirmatory outcomes have been performed by simulations and the frequentist method based on the power and level of significance of a test. For each primary confirmatory outcome, we have generated data from the distribution assumed for the combustible cigarette smokers and the distribution for the iQOS with HeatSticks smokers (based on our assumptions of how their changes in respiratory symptoms prevalence, proportions of participants who walk less than 450 meters, and annual exacerbation rate might be different if switched from combustible cigarettes to iQOS with HeatSticks). We have used R [19] for simulations (1000 simulations per each primary confirmatory outcome variable) and fitting a generalized linear mixed-effects model (GLMM) on simulated data (function “glmer” in the package “lme4”). For sample size calculation, we have used a power value of 80%, two-sided significance level (alpha) 1.7% that accounts for multiple hypotheses testing, and 1:2 ratio for sample sizes of the experimental and control cohorts.

Then, we have adjusted the sample size for anticipated proportion of dropouts (taking into consideration a 10% annual dropout rate and the fact that already collected data relating to any participant who stops the study early will be analyzed). Sample size calculations are presented in Table 1.

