### Study Procedures

#### Recruitment

We will select 800 current smokers and 400 users of iQOS with HeatStick based on the inclusion criteria. The recruitment strategy for smokers of combustible cigarettes and participants who use iQOS with HeatStick includes word-of-mouth communication to friends and spouses of individuals who participated in the cross-sectional study, advertisements, social media engagement (ie, Facebook, Instagram, WhatsApp chats), and outreach to community groups. In addition, we will recruit users of iQOS with HeatSticks at iQOS stores in Almaty, Kazakhstan.

To achieve comparability of comparison groups at baseline, the matched-pair cohort study design will be implemented, where a pair contains one iQOS with HeatSticks user and two conventional cigarette users. The following variables will be utilized for matching: gender, age (±3 years), education (as a proxy for socioeconomic status), and number of pack-year (±5 pack-years) as the baseline exposure level (number of pack-year).

Once potential participants who meet inclusion criteria are identified, they will undergo further medical assessment at the KAPM COPD Center to test for exclusion criteria and to start baseline comprehensive assessment.

The study will include (1) baseline comprehensive assessment at outset of the study during the enrollment period, which is expected to last for about 6 months (4^th^quarter of 2017 to 1^st^-3^rd^quarters of 2018); (2) annual comprehensive assessments at 2^nd^-4^th^quarters of 2018-2022; (3) periodic prospective case finding and exacerbation history assessment on quarterly basis (every 3 months), semiannual, and annual basis; and (4) continuous COPD case-finding activities based on patient self-assessment and professional clinical assessment during periodic visits to KAPM dedicated primary care unit.

**Table 1 table1:** Sample size calculations.

Primary confirmatory variable	Estimated value of outcome variable in exposure group	Estimated value of outcome variable in control group	Sample size exposed/ nonexposed	Adjusting sample size for anticipated dropouts
Symptomatic smokers defined by CAT ≥10	17%	42.8%	23/46	31/62
6MWT <450 m	11%	16.7%	260/520	347/694
Annual exacerbation rate	0.05	0.1	255/510	340/680

Baseline comprehensive assessment at outset of the study (4^th^quarter of 2017) and annual assessments (4^th^quarters of 2018-2020) will include the following:

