#### Assessment Test for Chronic Obstructive Pulmonary Disease

The CAT is a validated, short (8-item) questionnaire to be completed by study participants. Despite the fact that CAT is designed for patients with COPD, it can be used to measure respiratory symptoms among all participants including those who have preserved pulmonary function [10]. The CAT has a scoring range of 0-40, with the cut-off point equaling 10.

**Table 2 table2:** Schedule of participants enrollment and baseline assessment, 2017-2018.

Test	Screening^a^	Baseline visit^b^
Informed consent process	X	
Review inclusion/exclusion criteria to determine study eligibility, including smoking status and iQOS use	X	
Review medical history	X	
Provide study requirements handout (explain study/visit requirements)	X	
Pregnancy test	X	X
Stanford 25 comprehensive clinical assessment		X
Spirometry (FVC^c^, FEV^d^, FEV1^e^, FEV1/ FVC, FEF^f^ 25-75, MEF^g^), bronchodilation test using salbutamol		X
CAT^h^		X
6MWT^i^		X
Short form-12 Quality of Life questionnaire		X
ECG^j^		X
Body mass index		X
Smoking status and exposures		X
Comprehensive physical assessment Stanford 25		X
Previous COPD^k^ exacerbations based on use of inhaled steroids, antibiotics, inhaled bronchodilators, steroids		X
Previous COPD exacerbations based on health care visits (office visits, admissions to emergency department or hospital)		X
Previous COPD severe exacerbations based on emergency department admission or hospitalizations		X
Laboratory testing for blood cholesterol level, CBC^l^ (25 parameters); HDL^m^, LDL^n^, triglycerides, C-reactive protein, fibrinogen, glucose, glycosylated hemoglobin		X
Biomarker testing for sRAGE^o^, ICAM1^p^, and CCL20^q^		X
Lung computer tomography		X

^a^Months –3 to 3.

^b^Months 0 to 3.

^c^FVC: forced vital capacity.

^d^FEV: forced expiratory volume.

^e^FEV1: forced expiratory volume in 1 second.

^f^FEF: forced expiratory flow.

^g^MEF: maximum expiratory flow.

^h^CAT: COPD Assessment Test.

^i^6MWT: 6-Minute Walk Test.

^j^ECG: electrocardiogram.

^k^COPD: chronic obstructive pulmonary disease.

^l^CBC: complete blood count.

^m^HDL: high-density lipoproteins.

^n^LDL: low-density lipoproteins.

^o^sRAGE:advanced glycosylation
end-product receptor.

^p^ICAM1: intercellular adhesion molecule 1.

^q^CCL20: macrophage inhibitory protein
3a.

**Table 3 table3:** Schedule of participants visits for data collection and monitoring, years 1-5.

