### Computer-Assisted Personal Interviewing

KAPM has developed an electronic data capture system in the form of its proprietary computer-assisted personal interviewing app. The app is available for tablet personal computers and will be modified to be implemented in the cohort study to collect, store, and transmit data related to a personal survey interview. The questionnaire will be designed to collect data on possible COPD risk factors including history of smoking, current smoking, level of smoking exposure (in pack-year), passive smoking, occupational and environmental hazards, including dusts, chemicals, and indoor fuel pollution. The questionnaire will contain covariates: age, gender, ethnicity, education, occupation, and self-reported morbidity. It will also include questions to address COPD exacerbations and to record the use of combustible cigarettes, iQOS with HeatSticks, electronic cigarettes, and other alternatives, as well as iQOS switch date.

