### Statistical Analysis and Data Management Plan

Appropriate descriptive statistics will be used to summarize required study elements overall and by cohort (eg, proportion, mean, standard error, median, and interquartile ranges). Exploratory graphical analysis will be done preliminary to numerical analysis. Histograms, two-dimensional scatterplots of raw data, will provide information on the univariate and bivariate distributions of the variables focusing on distribution of variables, relation between the variables, whether it is linear or nonlinear, etc. In addition, preliminary graphs will screen raw data by highlighting obvious data errors. Spaghetti plots, scatterplots of dependent variable scores versus the time variable with a separate line for each person, will explore likely models, especially whether effects are linear or not.

Generalized estimating equations (GEE) and GLMM will be used to assess the effect of exposure on outcome variables. Both GEE and GLMM are used to account for within-person correlation of observations due to repeated measures. GEE uncovers the population average effect of a covariate, whereas GLMM estimates the individual specific effect. For binary confirmatory outcomes, CAT score ≥10, and inability to walk 450 meters on the 6MWT, the logit transformation will be utilized as the model link function. To model the annual exacerbation rate (count data), we will use the logarithm transformation and the Poisson or quasi-Poisson distribution depending on mean-variance relationship.

Presence of the statistically significant “time by group” interaction coefficient in GEE/GLMM will be our focus. It will demonstrate that the primary outcomes in two cohorts will have been changed significantly and provide statistical evidence for the harm reduction hypotheses.

To adjust for confounders, we will examine distributions of all covariates in the exposed and control group and will use Cohen effect sizes [26] to identify whether participants’ characteristics are different between groups at baseline. The impact of a potential confounder will be confirmed on whether the adjustment for the confounding variable changes the estimate of association.

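### The exposed cohort switched to iQOS before enrolment, but the study is sized as if the association were 1 at baseline and its focal test sees only later divergence

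*Protocol article*

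**What the plan says.** - **Who is exposed.** The Study Design section enrols people "who switched to and predominantly use the heated tobacco product iQOS with HeatSticks (exposure group", where predominant means more than 70% use. Under Recruitment, "we will recruit users of iQOS with HeatSticks at iQOS stores in Almaty". Table 2 places this item at screening: "Review inclusion/exclusion criteria to determine study eligibility, including smoking status and iQOS use". No limit is set on how long ago the switch took place. Matching uses gender, age, education and pack-years, not time since switching.
- **How the study is sized.** The Sample Size Calculation section takes associations seen in people who stopped smoking 1-5 years ago and applies them to iQOS users at the final visit. Of that abstinence range it says: "This is comparable with the length of the cohort study (5 years) that we propose". The path is then set: "We also assume that these associations will increase steadily from 1 to the above-indicated values". The final values are an odds ratio of 0.27 for CAT ≥10, 0.62 for walking under 450 m, and a rate ratio of 0.5 for exacerbations.
- **What is tested.** In the Statistical Analysis and Data Management Plan section, the time-by-group "interaction coefficient in GEE/GLMM will be our focus". A significant coefficient is to "provide statistical evidence for the harm reduction hypotheses".
- **What is recorded.** The interview app collects use of each product "as well as iQOS switch date". No primary analysis is said to use that date.

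**The concern.** The sizing describes people who switch at baseline. The cohort consists of people who switched at unknown, mixed times before it. With the usual group main effect, any benefit already gained sits in that main effect, where it cannot be told apart from selection into iQOS use. The interaction sees only what happens afterwards.

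The Introduction and Discussion hypothesise a difference in level: fewer symptoms, better exercise capacity and fewer exacerbations in iQOS users. A real benefit that is present at enrolment and stable would satisfy that hypothesis and still give an interaction near zero. The plan names the interaction as its evidence for harm reduction and does not say how a null result is to be read, so such a benefit could be reported as no harm reduction.

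**Working it through.** **1. Does the stated sample size depend on starting at 1?** Inputs from the Sample Size Calculation section and Table 1: two-sided alpha 0.017, power 80%, ratio 1:2, proportions 17% v 42.8% (CAT) and 11% v 16.7% (6MWT).

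A single comparison at the final visit needs, per exposed group, n = [z_α √(1.5·p̄·q̄) + z_β √(p₁q₁ + p₂q₂/2)]² / (p₂ − p₁)², with z_α = 2.3867, z_β = 0.8416 and p̄ = (p₁ + 2p₂)/3.
- CAT: p̄ = 0.342, n = 50. Table 1 has 23.
- 6MWT: p̄ = 0.148, n = 589. Table 1 has 260.

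An interaction model, logit p = b₀ + b₁·group + b₂·time + b₃·group·time, with the odds ratio moving log-linearly from 1, gives 23 (CAT) and 262 (6MWT) with six annual visits and an exchangeable within-person correlation of 0.68. With five visits and a correlation of 0.715 it also gives 23 and 262. The correlation is my assumption, so this shows consistency, not proof.

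The exacerbation figure (255) does not reproduce: 597 to 1098 with a group main effect, 222 to 285 without. I base no power figure on it.

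The dropout adjustment is N/0.75 throughout (260/0.75 = 346.7), and 347 + 694 = 1041.

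**2. Loss if part of the effect precedes baseline.** Let L be the final log odds or rate ratio and f the share present at baseline. The documents give no value for f. On a straight path over T years, b₁ = fL and b₃ = (1 − f)L/T, so the tested coefficient shrinks by (1 − f). With the standard error unchanged and 2.3867 + 0.8416 = 3.228:

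power ≈ Φ[3.228(1 − f) − 2.387], plus a negligible opposite tail except near f = 1.

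| f | 3.228(1 − f) − 2.387 | Power | N multiplier 1/(1 − f)² | OR left to detect, 6MWT (0.62^(1−f)) |
|---|---|---|---|---|
| 0 | 0.841 | 80% | 1 | 0.62 |
| 0.25 | 0.034 | 51% | 1.8 | 0.70 |
| 0.5 | −0.773 | 22% | 4 | 0.79 |
| 0.75 | −1.580 | 6% | 16 | 0.89 |
| 1 | −2.387 | 1.7% (both tails) | none suffices | 1 |

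**3. Slack at 400/800.** Set 1/(1 − f)² equal to planned N over dropout-adjusted N:
- 6MWT: 400/347 = 1.15, so 80% is kept up to f = 1 − 1/√1.15 ≈ 0.07.
- Exacerbations, taking Table 1 at face value: 400/340 = 1.18, f ≈ 0.08.
- CAT: 400/31 = 12.9, f ≈ 0.72.

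This is generous, because the protocol reserves the extra participants for product switching, quitting and confounder adjustment.

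The information-matrix calculation agrees. With 400/800, 10% annual dropout, six visits and correlation 0.68, power at f = 0, 0.25, 0.5, 0.75 and 1 is 81%, 52%, 22%, 6% and 1.7% for 6MWT, and about 100%, 100%, 99.9%, 63% and 1.7% for CAT. Over correlations from 0.2 to 0.8, 6MWT power runs from 41% to 96% at f = 0 and from 9% to 36% at f = 0.5.

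**4. Translating years since switching into a loss.** This needs an assumed shape. Suppose benefit accrues log-linearly and stops 5 years after switching, and everyone switched s years before baseline. The fitted least-squares slope relative to a full ramp is then:
- visits at years 0-5: 0.929, 0.857 and 0.629 for s = 0.5, 1 and 2; power 73%, 65% and 36%;
- visits at years 0-4, as in Table 3 (baseline plus the first quarter of Years 2-5): 1.000, 1.000 and 0.80; power 80%, 80% and 58%, since 3.228 × 0.80 − 2.387 = 0.195.

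Without a plateau, the slope is the same for any s.

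**The case against.** **The interaction may be the intended target.** The Study Design goal refers to outcomes across time, and the Discussion speaks of differing trends. In a non-randomised cohort, separating a baseline gap that is partly selection from later divergence is defensible and conservative. This stands, and is a reason to keep the interaction. It does not make a null interaction informative about benefit gained earlier.

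**Other analyses are planned.** The protocol calls the interaction its focus, not its only test. It also lists intention-to-treat, censored, propensity-score and period-weighted dose analyses. That stands too, so it would be too strong to say that only change is examined. None of these is named as the confirmatory test, however, and none is said to use time since switching.

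**The starting value of 1 is not labelled as baseline.** True, but the end values are fixed at the final visit after 5 years, and no other starting point reads naturally.

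**Stronger readings that the documents do not support.**
- A reader might infer that power falls to 73%, 65% or 36% for switching 0.5, 1 or 2 years earlier. Those figures need visits at years 0-5 and a plateau at 5 years. The documents state no plateau, and on Table 3's visits there is no loss at 0.5 or 1 year.
- A reader might infer that the planning study shows the full benefit soon after stopping. It reports one pooled cross-sectional prevalence for people 1-5 years after stopping, which says nothing about timing.
- A reader might infer that a linear time-since-switch term should replace the interaction. With a common lag s that term equals s·group + group·time, so it recovers nothing if the group term stays. If the group term is dropped, baseline confounding enters the estimate.

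**Conclusion.** The mismatch is real: established users are enrolled, the association is assumed to start at 1, and the focal test is blind to anything gained before enrolment. Given the plan's final-visit associations, 80% power is conditional on no effect at baseline. Power falls to about 51%, 22% and 1.7% if a quarter, a half or all of the final log effect is already present.

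These are scenarios, since time since switching is not given. They assume a straight path on the log scale, an unchanged standard error and a group main effect in the model. If that main effect were left out, the baseline gap would distort the interaction instead. If the effect keeps growing log-linearly at the planned yearly rate without a plateau, the slope is unaffected.

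The consequence is greatest for 6MWT, which sets the total and has little slack, and much smaller for CAT at 400/800. The interaction remains a valid test of divergence after enrolment. What needs correcting is the power statement and the inference drawn from a null result.

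**What to change.** Keep the time-by-group interaction as the test of divergence after enrolment, and make four changes before analysis:

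1. Report beside it the confounder-adjusted group contrast at baseline and the adjusted group difference at the final visit. State that the baseline gap mixes earlier benefit with selection.
2. State that a null interaction alone is not evidence against harm reduction.
3. Prespecify a supportive analysis using the recorded switch date, such as the interaction within strata of time since switching at baseline (under versus over 12 months).
4. Restate the 80% power as conditional on an association of 1 at baseline, and rerun the existing simulation for several starting values.

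No new visits or data are needed. The cost is some extra analysis and simulation work, recall error in the switch date, and a less favourable stated power.
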